### Randomization and Allocation of Participants

After completing the control period, the participants will be stratified by their sex and 1RM values and randomly allocated in equal numbers to the three intervention groups. Then, the treatment applied to the subjects’ legs will be determined by coin toss.

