## Methods/Design

### Experimental Approach

The present project and study protocol were registered in clinicaltrials.gov (ID: NCT03724461, October 30th, 2018) and approved by the Clinical Research Ethics Committee of the Complejo Hospitalario de Toledo (Spain). The study protocol will be conducted following the SPIRIT (Standard Protocol Items: Recommendations for Interventional Trials) statement (Chan et al., 2013). The intervention and data collection will be conducted at the University of Castilla-La Mancha, Toledo (Spain). This is a within-person randomized trial, including an 8-week control period followed by 12 weeks of PRT (Figure 1). The mean changes observed during the 8-week control period will be quantified to determine the possible extent of spontaneous changes in all outcome measures. After completing the control period, the participants will be randomized to one of the following study arms based on the treatment applied to their lower-limbs during the 12-week PRT program: (i) one leg will perform a light-load PRT and the other leg will not perform any exercise; (ii) one leg will perform a heavy-load PRT and the other leg will not perform any exercise; and (iii) one leg will perform a heavy-load PRT and the other leg will perform a light-load PRT. Assessments will be conducted at baseline (week 0), at the end of the control period (week 8), and following the 12-week PRT (week 20).

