### Participants

The sample size was determined by an *a priori* power analysis using G^∗^Power v3 software for MS Windows^®^ (Faul et al., 2007). The effect size value used for calculations was *d* = 0.25 based on a previous study comparing peak power adaptations after a 12-week heavy- vs. light-load PRT in older adults (de Vos et al., 2005). Then, we considered three levels for the between-subject factor (i.e., one for each study arm) and three levels for the within-subject factor (i.e., three repeated measures) setting the alpha error probability at 0.05, a 1−β of 0.95 and assuming a correlation among repeated measures of *r* = 0.8. The model indicated a minimum total sample size of 24 individuals, but considering a 25% dropout rate, we have decided to enroll at least 30 participants in total. People aged 65 years and over, non-institutionalized and without serious mobility limitations will be encouraged to participate. Principally, the volunteers will be recruited among participants involved in non-exercise studies previously conducted by our research group, local advertisements posted in public places and informative talks about healthy aging. After accepting to participate, the volunteers will undergo a physical examination by a geriatrician. The criteria for exclusion are: (i) frailty status (Fried et al., 2001) or low levels of physical function (i.e., Short Physical Performance Battery <7 points) (Guralnik et al., 1994), (ii) neurological, musculoskeletal, or other disorders that might preclude subjects from completing the resistance training and all performance tests, (iii) uncontrolled hypertension, unstable or exercise-induced angina pectoris or myocardial ischemia or any other medical condition that would interfere with testing or increase subjects’ risk of complications during exercise, (iv) history of regular resistance exercise during the previous 3 years, and (v) total or partial knee replacement (i.e., prosthesis). All participants will be informed orally and in written form about the purpose, procedures, benefits, risks, and potential discomfort related to study participation before signing a consent form. This study will be conducted in accordance with the Helsinki declaration.

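### Legs are assigned by independent coin toss after person-level stratification, which leaves avoidable chance imbalance between stronger and weaker legs; balancing legs within arm would remove it at almost no cost

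*Protocol article*

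**What the plan says.** Under Randomization and Allocation of Participants, the article says that after the control period participants will be "stratified by their sex and 1RM values and randomly allocated in equal numbers to the three intervention groups". The next sentence deals with the leg: "Then, the treatment applied to the subjects’ legs will be determined by coin toss". The restrictions named, strata and equal arm sizes, act on people. None is named for legs.

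Under Experimental Approach, two arms train one leg (light load in one, heavy load in the other) and leave the other leg unexercised. In the third arm "one leg will perform a heavy-load PRT and the other leg will perform a light-load PRT". Treatment is therefore given to legs, and the Statistical Analysis section analyses changes per leg. Both mixed models have treatment as fixed factor, participant as random factor and the baseline value as covariate, and both bring in the same legs' change over the control period. Neither has a term for stronger or weaker leg. The leg-press 1RM is measured one leg at a time and is available at week 8, before allocation.

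**The concern.** The Introduction justifies the unilateral design by its gain in power from removing variation between people. That gain is fullest when the two legs of a person are exchangeable apart from treatment. If stronger and weaker legs respond differently to training, an uneven spread of treatments over them adds noise to heavy minus light (goal 1) and to the comparison of untrained legs between the two single-leg arms (goal 2). Stratifying people on 1RM cannot prevent this, because the leg is chosen afterwards. With arms this small, independent tosses often give uneven splits. At stake is some precision in the main comparison of a small trial, and a baseline table that may look lopsided.

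**Working it through.** **Arm size.** The plan says: "The model indicated a minimum total sample size of 24 individuals, but considering a 25% dropout rate, we have decided to enroll at least 30". Its 24 reproduces for the within-between interaction with Cohen's f = 0.25, three groups, three measures, r = 0.8 and alpha 0.05: noncentrality 0.25² × 24 × 3 / (1 − 0.8) = 22.5 on 4 and 42 df, power 0.965. Equal allocation gives 30/3 = 10 per arm enrolled and 24/3 = 8 evaluable.

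**Chance of an uneven split.** Assume a fair, independent coin. The number of people in an arm whose stronger leg gets a given treatment is Binomial(n, 0.5). For at least one of three arms, use 1 − (1 − p)³.

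| Split | One arm | At least one of three |
|---|---|---|
| n = 10, not exactly 5:5 | 75.4% | 98.5% |
| n = 10, 7:3 or worse | 352/1024 = 34.4% | 71.7% |
| n = 10, 8:2 or worse | 112/1024 = 10.9% | 29.4% |
| n = 8, 6:2 or worse | 28.9% | 64.1% |

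Goal 1 pools 20 heavy-load and 20 light-load legs. Their counts of stronger legs differ by 4 or more with probability 36.9%. For goal 2, the share of stronger legs differs between the two single-leg arms by 0.3 or more with probability 26.3%.

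**Legs differ only through their starting value.** In a simulation of heavy minus light (assumed strength asymmetry 0.4 to 0.8 SD, slope of change on baseline −0.2 to −0.4, 1,500 runs per setting), bias was about 0 throughout. Without the covariate, the coin toss raised the standard error by about 2 to 7%. With it, the standard error was 0.126 to 0.129 under the coin toss and 0.127 to 0.129 under balance, so there was no consistent loss.

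**Legs also differ in training response.** Let δ be the stronger-minus-weaker difference in training change not captured by baseline, in SD of change, and ρ the correlation of change between a person's two legs. The documents give neither, so both are assumptions.

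- Sampling variance of heavy minus light: 2(1 − ρ)/n within the third arm and 2/n between the two single-leg arms. The optimal weight on the third arm is w = 1/(2 − ρ).
- Variance added by the coin toss: δ²/n in the third arm and δ²/(2n) between the single-leg arms.
- Relative increase in the variance of the combined estimate: δ² × [1 + (1 − ρ)²/2] / [2(1 − ρ)(2 − ρ)]. Arm size cancels.

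At ρ = 0.5 the multiplier of δ² is 1.125/1.5 = 0.75. With δ = 0.3, √(1 + 0.75 × 0.09) = 1.033. With δ = 0.5, √(1 + 0.75 × 0.25) = 1.090.

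| ρ | Multiplier | SE increase, δ = 0.3 | SE increase, δ = 0.5 |
|---|---|---|---|
| 0 | 1.5/4 = 0.375 | 1.7% | 4.6% |
| 0.5 | 0.75 | 3.3% | 9.0% |
| 0.7 | 1.045/0.78 = 1.34 | 5.9% | 15.5% |

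Simulation of the goal 1 model with the baseline covariate gave about 3 to 4% at δ = 0.3 and 5 to 10% at δ = 0.5, in line with the middle row. With δ = 0 the increase is zero.

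For goal 2 the relative increase is (δ²/2n)/(2/n) = 0.25δ². The standard error grows by √(1 + 0.25 × 0.09) − 1 = 1.1% at 0.3 and √(1 + 0.25 × 0.25) − 1 = 3.1% at 0.5.

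**After the change.** Balanced assignment gives 5:5 in an arm of 10, so the chance of 7:3 or worse falls from 34.4% to 0%. The sample size does not change.

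**The case against.** The strongest reply is that the analysis already deals with this. Both models adjust for the baseline value, most naturally read as each leg's own starting value of the outcome analysed. That is a finer measure of how strong a leg is than a stronger/weaker flag from leg-press 1RM, and for outcomes such as muscle architecture the flag may say little. This stands for everything that works through the starting value, as the simulation shows. It does not cover leg preference or a difference in response beyond baseline. The same-leg control period does not cover these either, because no training takes place in weeks 0 to 8.

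It is also fair to say that 72% refers to any one of three arms. In a given arm a marked imbalance is the less likely outcome, and only net differences between compared legs matter. And the article is condensed: the full protocol may restrict the toss, define the 1RM used for stratification and say how tosses are recorded. Those omissions are not held against the plan here. The point rests on the method that the article does state.

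Two stronger readings are tempting. A reader might infer that the heavy versus light comparison is biased. It is not: a fair toss gives no bias in expectation. A reader might also take a bad split in the third arm, multiply it by an assumed leg difference and set the product against the planning value of 0.25. The documents do not support that. Goal 1 pools the third arm with the other two, the baseline covariate is ignored, no leg difference in change is given, and 24 reproduces only if 0.25 is Cohen's f, although the article labels it d. A shift in SD units is not a fraction of f.

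**Conclusion.** The point holds as a low-cost design improvement, not as an error or a threat to validity. Chance imbalance of stronger and weaker legs is common under the stated method: 34% per arm and 72% in at least one arm for 7:3 or worse, given 10 per arm and a fair coin. Its cost is avoidable random error, about 3 to 10% in the standard error of heavy minus light if legs differ in training response by 0.3 to 0.5 SD beyond baseline. The loss is smaller if the two legs' changes are weakly correlated, larger if they are strongly correlated, and nil if there is no such difference. The imbalance probabilities are exact. The precision loss rests on assumptions that the documents neither support nor exclude.

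**What to change.** Replace the coin toss with a computer-generated list, made before allocation, that assigns arm and leg rank together. Within each arm, half of the participants have the treatment on the stronger leg and half on the weaker; in the third arm, half have heavy load on the stronger leg. Rank the legs by the week-8 unilateral 1RM. With an odd arm size the split can differ by one.

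Reflect the factor in both mixed models with one term for stronger versus weaker leg, applied to the training-period change, since control-period changes contain no training response. Without this term, the balanced estimate is more precise but the leg difference stays in the residual variance, so the reported standard error does not show the gain.

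The cost is slightly more work to set up the randomisation, a sentence or two in the protocol and one extra model term. Sample size, visits and measurements are unchanged.

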### Interventions

All participants will complete a 12-week PRT programs targeting the lower limbs twice a week (total of 24 sessions). Training sessions will be performed on a horizontal leg press device that includes a weight stack system (Selection MD, Technogym, Italy) where participants will execute unilateral repetitions. For standardization, participants will be requested to fully extend their leg from a common starting position (knee and hip joint angles of 90° and 70°, respectively; full extension = 180°). Each exercise session will start with a 5-min warm-up on a cycle-ergometer at a low self-regulated intensity and a crank velocity of approximately 70 rpm. Then, the lower limbs to be trained will undergo a specific warm-up consisting of one set of 10 repetitions at 50% of the individual one repetition maximum (1-RM), with repetitions executed at submaximal velocity. The PRT performed with light loads (LL-PRT) will consist of six sets of 12 repetitions using a load equivalent to 40% 1-RM, whereas heavy-load PRT (HL-PRT) will comprise six sets of six repetitions with a load equivalent to 80% 1-RM. Therefore, the total volume × load will be matched between the training programs to minimize bias related to unequal training volumes. In addition, the 1-RM will be re-assessed in 4-week intervals to adjust training loads and ensure progressive overload. For both training programs, the participants will be instructed and verbally encouraged to perform the concentric phase of each repetition as fast and strong as possible (i.e., ballistic approach), whereas during the eccentric phase the load will be lowered in a controlled manner in 3 s and 2 s for LL-PRT and HL-PRT, respectively. These unequal durations serve to balance the greater volitional effort required to retain a heavier load compared with a light load during the eccentric phase (Rodriguez-Lopez et al., 2020). Sets will be interspersed by 2-min rest periods. In subjects in whom both lower limbs will be trained (i.e., HL-PRT vs. LL-PRT group), an additional rest period of 1-min will be included between each leg, and the leg trained first will alternate between sessions. To warrant adequate recovery, all training and testing sessions will be separated by a minimum of 48 h. Participants will be required to attend to at least 80% of sessions. Those unable to participate for 10 days or more will be excluded from the study. Furthermore, subjects will be asked to maintain their regular physical activity levels and diet, and to inform study administrators about any changes in their medications. All training sessions and tests will be attended individually, supervised by an experienced sport scientist, and conducted approximately at the same time every day.

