### Statistical Analysis

Data will preferentially be presented as mean ± standard deviation. Normality of distribution will be assessed by the Shapiro–Wilk test and log-transformed in case of non-normal distribution. As preference, the outcomes will be registered as the absolute (Post – Pre) and relative [(Post – Pre)/Pre] change during the 8-week control period and the 12-week PRT program. Given the hierarchical structure and correlated data contained in our investigation (each participant will contribute to observations in two different groups), the existence of partially paired data must be considered for comparison purposes. Thus, linear mixed effect models will be used to assess the goals proposed for the present investigation. To assess the adaptations provoked by two volume × load-matched PRT programs using heavy vs. light loads in older adults (goal 1), changes noted in the legs undergoing HL-PRT and LL-PRT (i.e., week 20-week 8) and those noted in the same legs during the control period (i.e., week 8-week 0) will be compared with treatment (HL-PRT vs. LL-PRT vs. control) as a fixed factor, participants as a random factor and baseline values as a covariate. To investigate the adaptations provoked by heavy- vs. light-load PRT on the contralateral limb in older adults (goal 2), changes noted in the contralateral non-exercising legs of those legs performing either HL- or LL-PRT (i.e., week 20-week 8) and those noted in the same legs during the control period (i.e., week 8-week 0) will be compared with treatment (HL-PRT vs. LL-PRT vs. control) as a fixed factor, participants as a random factor and baseline values as a covariate. The models will be calculated considering maximum likelihood estimation and the best-fitting covariance structure. Bonferroni corrections will be applied for the *post hoc* pairwise comparisons and the Cohen’s *d* effect sizes will be calculated and classified as trivial (0.20), small (0.20–0.49), moderate (0.50–0.79), and large (>0.8) (Cohen, 1988). Potential adverse events and drop-outs will be compared between groups by Chi-squared tests. All statistical analyses will be performed using IBM SPSS Statistics for Windows Version 24.0 (IBM Corp. Armonk, NY, United States), and the level of significance will be set at α = 0.05.

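### The 10-day absence rule excludes randomised participants who can still meet the 80% attendance requirement, and leaves the between-person heavy-versus-light contrasts open to selection bias

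*Protocol article*

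**What the plan says.** The Interventions section of the protocol article describes 12 weeks of training "targeting the lower limbs twice a week (total of 24 sessions"), and adds that "all training and testing sessions will be separated by a minimum of 48 h". It then sets two participation criteria in consecutive sentences. The first is "Participants will be required to attend to at least 80% of sessions"; no consequence is given for falling short. The second is "Those unable to participate for 10 days or more will be excluded from the study". The text does not say whether the 10 days are consecutive or cumulative.

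On timing, Randomization and Allocation of Participants says: "After completing the control period, the participants will be stratified by their sex and 1RM values and randomly allocated in equal numbers". Any absence from training therefore comes after allocation.

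Under Statistical Analysis, goal 1 compares "changes noted in the legs undergoing HL-PRT and LL-PRT (i.e., week 20-week 8) and those noted in the same legs during the control period". Goal 2 does the same for the untrained contralateral legs. Both use linear mixed models fitted by maximum likelihood, with participant as a random factor. The only stated handling of drop-outs is a Chi-squared comparison between groups. The Participants section sets enrolment at 30 or more, "considering a 25% dropout rate".

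**The concern.** The second criterion takes people out of the study, not only out of training. Its trigger lies downstream of randomisation and may depend on the allocated load: the Harms section itself expects early muscle soreness and provides for exercise-related adverse events. A person who leaves under this rule is not measured at week 20, and no later analysis plan can recover a measurement that was never taken.

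What is at stake is the comparability of the randomised groups in those contrasts that depend on it. If the people lost on one load would have responded differently from those kept, and this differs by load, the heavy-versus-light difference among those kept is not the difference among those randomised. The rule also spends sample size on people whom the plan's attendance standard would have counted as sufficiently trained, in a trial with about 10 participants per arm.

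**Working it through.** **Inputs (protocol article).** 12 weeks at 2 sessions a week; minimum spacing 48 h; attendance of at least 80%; exclusion at 10 days or more (Interventions). Three equal arms (Randomization and Allocation). Outcome is the week 20 minus week 8 change (Statistical Analysis).

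**1. Attendance threshold.** 12 × 2 = 24 sessions, as stated. 0.80 × 24 = 19.2, so 20 sessions must be attended and 4 may be missed.

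**2. Sessions lost to one absence.** An absence window was slid across the 12-week calendar for every twice-weekly pattern with sessions 2 to 5 days apart, assuming all other sessions are attended.

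| Absence, calendar days | Sessions missed | Attendance |
|---|---|---|
| 10 or 11 | 2 to 4 | 22/24 = 91.7% to 20/24 = 83.3% |
| 12 or 13 | 3 to 4 | 21/24 = 87.5% to 20/24 = 83.3% |
| 14 | 4 | 20/24 = 83.3% |
| 15 | 4 to 5 | 20/24 = 83.3% to 19/24 = 79.2% |

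The four-session case arises, for example, on a Monday and Wednesday schedule when the absence begins on a Monday (days 0, 2, 7 and 9). Every single absence of 10 to 14 days meets the 80% requirement yet triggers exclusion. The shortest absence that can break the 80% requirement is 15 days. If the rule meant 10 missed session days, attendance would be 14/24 = 58.3% and both criteria would fail together, but the sentence speaks of days.

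**3. What the models lose.** With no week-20 value there is no training-period change. At most the control-period change of that person stays in. Maximum likelihood deals with missingness that the observed data explain; it does not restore the randomised comparison if absence depends on the unobserved training response. Contrast by contrast:

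- Goal 1, heavy versus light across the two single-leg arms: between-person, exposed.
- Goal 1, heavy versus light within the two-leg arm: exclusion removes both legs, so the pair stays balanced, though in a selected group.
- Goal 2, heavy versus light in contralateral legs: between-person, exposed. The two-leg arm has no untrained leg to contribute.
- Both goals, training versus control period: same legs, so within-leg.

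**4. Illustration (all inputs assumed).** Let p be the proportion excluded in an arm and δ the amount by which those excluded would have responded less than those kept. The mean among those kept is too high by δp, so the single-leg contrast shifts by δ(p_heavy − p_light).

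- p_heavy = 0.30, p_light = 0.10, δ = 0.5 SD: 0.5 × 0.20 = +0.10 SD.
- Equal proportions: 0.
- Proportions reversed: −0.10 SD.

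For the overall goal 1 estimate, assume equal arms, an equal deficit in both legs of those excluded from the two-leg arm, and inverse-variance pooling. With correlation ρ between the two legs' changes, the weight on the single-leg contrast is (1 − ρ)/(2 − ρ):

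- ρ = 0: weight 0.50, shift 0.05 SD.
- ρ = 0.5: weight 0.333, shift 0.033 SD.
- ρ = 0.8: weight 0.167, shift 0.017 SD.

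The contralateral heavy-versus-light contrast in goal 2 has no paired arm to dilute it. If the same inputs held for untrained legs, the full 0.10 SD would apply.

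**The case against.** **The two sentences need not contradict each other.** A floor on total attendance and a ceiling on absence can apply together and catch different people: five scattered missed sessions fail the first and not the second. This stands. A reader might infer a strict contradiction, but the text does not make the 80% figure the sole standard. What remains is that the second rule removes people who satisfy the first, with no reason given and the counting of days undefined.

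**Most of the design is protected.** The control-period contrasts are within-leg and the two-leg arm is paired. This also stands. A reader might conclude that all of goal 2 rests on randomisation, or that the whole trial becomes a completers' comparison. The first is wrong for the training-versus-control part. The second goes beyond the text, which names no analysis set, and a separate analysis plan may define one.

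**The aim concerns adaptations to the programmes, so an adherence-based question is defensible.** It is, but it can be answered with a per-protocol set while everyone is still measured.

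**Safeguards exist.** Drop-outs are compared between groups, and the Harms section sends exercise-related events to a joint decision on further participation. A count comparison with about 10 per arm has little power and repairs nothing. The joint decision is not reconciled with the unconditional 10-day sentence.

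**The size is unsupported.** Correct. Nothing in the document supports 30%, 10% or 0.5 SD, and the Harms section expects minimal injury risk and soreness that fades. Nor should 0.10 SD be read as 40% of the planned 0.25. That value is labelled d, but the stated sample size of 24 reproduces when it is entered as f (interaction test; power 0.965 at 24), which is a different scale. Taking 25% of 30, or 7 to 8 people, as the number this rule would remove is also unsafe: the 25% is a general allowance and can include losses before randomisation.

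**Conclusion.** The concern holds in a limited form. As written, the protocol excludes participants after randomisation on a criterion that training can influence, and a single absence of 10 to 14 days triggers it at 83.3% to 91.7% attendance. This assumes calendar days, one absence and no other missed sessions. The consequence is missing week-20 data, which exposes the heavy-versus-light contrast between the single-leg arms and the contralateral heavy-versus-light contrast to selection. The paired arm and the control-period comparisons are much less affected.

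Neither the size nor the direction of a bias can be derived from the document. The illustration gives 0.10 SD between single-leg arms and 0.017 to 0.05 SD in the pooled goal 1 estimate; it shows scale only. There is little room for avoidable losses: 30 × 0.75 = 22.5 is already below the 24 required. This is worth correcting because the remedy is cheap, not because a large bias has been shown.

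**What to change.** - Separate stopping training from leaving the study. Invite every randomised participant to the week-20 assessments already scheduled, subject to their consent and to clinical clearance for the tests.
- Analyse all available data by randomised arm and leg in the planned mixed models.
- Use the attendance criteria only to define a per-protocol set for a sensitivity analysis.
- Reconcile the 80% and 10-day sentences with each other and with the Harms section: say whether the days are consecutive or cumulative, and what follows from each criterion.

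No rule on absence or on continuing training is proposed here; those remain clinical decisions.

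The cost is a change of wording and a few more week-20 assessments, each spread over three separate days. The estimated training effect may be somewhat smaller once people who trained less are included.
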